## Abstract

**Introduction:**

The WHO End-TB Strategy calls for the development of novel diagnostics to detect tuberculosis (TB) earlier and more accurately. Better diagnostics, together with tools to predict disease progression, are critical for achieving WHO End-TB targets. The **E**arly **R**isk **A**ssessment in TB Contacts by new diagno**S**tic t**E**sts (ERASE-TB) study aims to evaluate novel diagnostics and testing algorithms for early TB diagnosis and accurate prediction of disease progression among household contacts (HHCs) exposed to confirmed index cases in Mozambique, Tanzania and Zimbabwe.

**Methods and analysis:**

A total of 2100 HHCs (aged ≥10 years) of adults with microbiologically-confirmed pulmonary TB will be recruited and followed up at 6-month intervals for 18–24 months. At each time point, a WHO symptom screen and digital chest radiograph (dCXR) will be performed, and blood and urine samples will be collected. Individuals screening positive (WHO symptom screen or dCXR) will be requested to provide sputum for Xpert MTB/Rif Ultra. At baseline, HHCs will also be screened for HIV, diabetes (HbA1c), chronic lung disease (spirometry), hypertension and anaemia. Study outcomes will be coprevalent TB (diagnosed at enrolment), incident TB (diagnosed during follow-up) or no TB at completion of follow-up. Novel diagnostics will be validated using fresh and biobanked samples with a nested case–control design. Cases are defined as HHCs diagnosed with TB (for early diagnosis) or with incident TB (for prediction of progression) and will be matched by age, sex and country to HHCs who remain healthy (controls). Statistical analyses will include assessment of diagnostic accuracy by constructing receiver operating curves and calculation of sensitivity and specificity.

**Ethics and dissemination:**

ERASE-TB has been approved by regulatory and ethical committees in each African country and by each partner organisation. Consent, with additional assent for participants <18 years, is voluntary. Attestation by impartial witnesses is sought in case of illiteracy. Confidentiality of participants is being maintained throughout. Study findings will be presented at scientific conferences and published in peer-reviewed international journals.

**Trial registration number:**

NCT04781257.Cite Now

Strengths and limitations of this studyRecruitment of highly infectious index cases aimed at maximising the number of tuberculosis (TB) diagnoses in the household contact (HHCs) cohort.Sequencing of *Mycobacterium tuberculosis* isolates from both index cases and HHCs allows confirmation of household transmission and, thus, determination of timing of the transmission event; resulting in more precise estimates of new test sensitivity compared with population-based cohorts with unknown timing of infection.Large sample size across three southern African countries with high HIV prevalence; including adolescents will ensure that study findings are generalisable to the clinically relevant population at high risk of TB compared with studies focused on adults only.Despite the large cohort of HHCs, the number of diagnosed TB cases will be small, limiting the power of the study and subgroup analyses such as by age and HIV status.Geographically limited to sub-Saharan Africa; therefore, results may not be generalisable to other populations, including those with lower HIV prevalence such as in South-East Asia or the Americas.

## Introduction

Tuberculosis (TB) remains a leading global public health problem, with an estimated 10 million new cases and 1.5 million deaths globally in 2020.^1^ In 2014, the World Health Assembly approved the WHO End-TB Strategy, aiming for a 90% reduction in TB incidence and 95% reduction in TB deaths by 2035.^2^ However, in 2019, three million TB cases (‘the missing millions’) remained undiagnosed and untreated globally, resulting in potentially avoidable morbidity, mortality and onward transmission. The COVID-19 pandemic has resulted in a large decrease in the number of people newly diagnosed with TB and reported. This has increased the diagnostic gap by a further 1.3 million, resulting in an estimated 4.2 million undiagnosed TB cases in 2020.^3^ Also, for the first time in a decade, TB deaths have risen, from an estimated 1.4 million in 2019 to 1.5 million in 2020, as a result of reduced access to and provision of essential TB services, including diagnostics during the COVID-19 pandemic.

Without an efficacious and safe vaccine, early detection and containment are the main tools to interrupt transmission and successfully control TB. Similar to SARS-CoV2, asymptomatic spreading of *M.tuberculosis* and subclinical but infectious disease states are a major concern in the control of airborne infectious diseases.^4^ Early and accurate identification of persons with TB, combined with identification of those at risk of progression to TB and provision of targeted preventive treatment, are critical to reducing TB-associated morbidity and mortality, and preventing onward transmission.

Currently available diagnostics such as sputum microscopy, mycobacterial culture and nucleic acid amplification tests are based on direct pathogen detection, thus requiring a high mycobacterial load; they, therefore, predominately target advanced TB when onward transmission and significant lung damage has occurred.^5 6^ Furthermore, for many patients with minimal or no symptoms, expectoration of high-quality sputum specimens remains challenging, limiting the accuracy of sputum-based tests. The same holds true for young children and people living with HIV.

The **E**arly **R**isk **A**ssessment in TB Contacts by new diagno**S**tic t**E**sts (ERASE-TB) study aims to fill this diagnostic gap by evaluating new sputum and non-sputum-based TB diagnostics for early TB detection (before onward transmission occurs) as well as tools for more accurate prediction of TB progression to allow for targeted preventive therapy.

## Methods and analyses

### Study objectives

ERASE-TB’s primary objectives are (1) to determine the sensitivity and specificity of novel diagnostics to detect TB, in particular, asymptomatic or minimally symptomatic TB, (2) to evaluate novel diagnostics for detection of likely TB progression and (3) to enhance the performance of novel diagnostics by simulating testing algorithms coupled with individual risk estimates from a mathematical model. The secondary objectives are (1) to determine the TB prevalence among household contacts (HHCs) of infectious TB index cases (ICs) at baseline and during 18–24 months follow-up, (2) to establish a biorepository of cryopreserved specimens from HHCs for future development and validation of diagnostic tests and (3) to assess the association of selected chronic disease conditions and TB among HHCs.

### Study endpoints

The study’s primary endpoints are the presence or development of TB among HHCs with the following possible scenarios of (1) prevalent symptomatic TB at baseline, (2) incident TB during follow-up and (3) remained healthy until study completion. An endpoint review committee will review the data and case classification before finalisation.

Through the sequencing of *Mycobacterium tuberculosis* (*Mtb*) isolates, cases of coprevalent or incident TB will be classified either as secondary, infected by the source case—the timepoint of infection will be known; or as infected by another, unknown source of infection, with an unknown timepoint of infection.

### Recruitment sites

Recruitment of ICs and HHCs at selected primary healthcare facilities and communities has commenced in Harare, Zimbabwe in March 2021, Maputo, Mozambique in August 2021, and Mbeya, Tanzania in September 2021. Partners of the ERASE-TB consortium are illustrated in figure 1. All three countries have a high TB incidence ranging from 100 to 499/100 000 population^1^ and HIV prevalence among adults aged 15 years and older of 5%–20%.^7^ The African research institutions have established collaborations with their respective National Tuberculosis Programs ensuring referral and appropriate follow-up of patients with TB. Figure 2 illustrates the geographic location of research institutions, healthcare facilities where recruitment is taking place, demographic characteristics of study populations and estimates on TB incidence and HIV prevalence.^8–15^

**Figure 1 F1:**
[figure not shown]
The ERASE-TB consortium. ERASE-TB, Early Risk Assessment in TB contactS by new diagnostic tEsts.

**Figure 2 F2:**
[figure not shown]
Location and characteristics of ERASE-TB study sites. The location of each study site is indicated by a red asterisk. Source data used within this figure are taken from the references.^7–15 40–42^ ERASE, Early Risk Assessment in TB contactS by new diagnostic tEsts; TB, tuberculosis.

### Study design

ERASE-TB is a non-interventional, longitudinal, prospective cohort study among HHCs aged ≥10 years exposed to highly infectious pulmonary TB ICs aged ≥18 years. Eligibility criteria are detailed in figure 3 and the study design is shown in figure 4. TB ICs are eligible if the bacterial load in their sputum is at least at the ‘medium’ level according to Xpert MTB/RIF or Xpert MTB/RIF Ultra, and they have received less than seven daily doses of anti-TB treatment before enrolment. This maximises the likelihood of culturing and storing *Mtb* isolates. The total study duration will be 36 months. This includes 12-month enrolment of ICs and HHCs, and 18-month to 24-month follow-ups of HHCs. Follow-up ends when a HHCs withdraws from the study, is lost to follow-up, dies or is diagnosed with TB and referred for treatment. Scheduled or unscheduled unwell visits can be conducted physically and/or telephonically in case of abnormal finding, for example, by abnormal digital chest radiograph (dCXR), or when a participant feels unwell in between scheduled follow-up visits.

**Figure 3 F3:**
[figure not shown]
Eligibility criteria and schedules of events for index cases and household contacts. A=depending on the time point of study enrolment and consequently on the duration available for follow-up, that is, 18 or 24 months, the follow-up visit at 24 months±30 days may be conditional; B=the follow-up visit by phone may be conducted after the last scheduled follow-up visit at 18 months±30 days or 24 months ±30 days to assess whether symptoms suggestive of TB have occurred, TB diagnosis has been made or anti-TB treatment has been initiated; C=unwell visits by phone or on-site may be conducted between scheduled follow-up visits if a participant presents at a recruitment healthcare facility with signs and symptoms suggestive of TB; D=coached spontaneous or induced sputum collection for storage at scheduled follow-up visit at 18 months±30 days or 24 months ±30 days, and for repetition of HIV testing if tested negative at baseline; E=coached spontaneous or induced sputum collection on the decision of the investigating team for testing by Xpert MTB/RIF Ultra if participant presents with signs and symptoms suggestive of TB; F=coached spontaneous or induced sputum collection in case of Xpert MTB/RIF Ultra positivity or strong clinical suspicion of TB for repetition of the Xpert MTB/RIF Ultra; G=in case of HIV positivity to be followed by the assessment of CD4 counts; H=CXR to be conducted at an unscheduled on-site unwell visit on the decision of the investigating team depending on the nature of symptoms reported, and the time elapsed since the last CXR including its findings; I=not to be conducted among pregnant women; J=stored venous blood includes 6 mL EDTA blood for whole blood and plasma, 4 mL serum and 2.5 mL PAXgene blood, all samples will be deep frozen for retrospective testing using new diagnostics as described in text; K=in case the evaluation of symptoms of a participant unable to present at a recruitment healthcare facility is required an unscheduled on-site or home visit will be arranged by phone, the resolution of symptoms can alternatively be addressed by phone; L=collection of PBMC at baseline and follow-up visit at 6 months±30 days is optional, thus will not be performed at each participating site and for each participant; M=in case the evaluation of symptoms of a participant unable to present at a recruitment healthcare facility is required or doubtful if required an unscheduled unwell visit by phone will be arranged, the resolution of symptoms can alternatively be addressed by phone; N=spirometry and/or diabetes (HbA1c) will be performed at scheduled follow-up visits at 6 months±30 days, 12 months ±30 days and 18 or 24 months±30 days if required or not performed at baseline, anaemia (Hb) will be performed at baseline and scheduled follow-up visits at 6 months±30 days, 12 months ±30 days and 18 or 24 months±30 days if possible; O=blood pressure measurement will be performed at baseline and scheduled follow-up visits at 6 months±30 days, 12 months ±30 days and 18 or 24 months±30 days; P=WGS to be performed once *Mtb* infection is confirmed and an isolate could be recovered. CD4, cluster of differentiation 4; CXR, chest radiograph; Hb, haemoglobin; HbA1c, glycated haemoglobin; IGRA, interferon gamma release assay; LAM, lioparabinomannan; MTB, *Mycobacterium tuberculosis*; MBLA, molecular bacterial load assay; PBMC, peripheral blood mononuclear cell; RIF, rifampicin; TAM-TB, T- cell activation marker tuberculosis; TB, tuberculosis; WGS, whole genome sequencing.

**Figure 4 F4:**
[figure not shown]
Study design. CXR, chest radiograph; FU, follow-up; HHC, household contact; IC, index case; MTB, *Mycobacterium tuberculosis*; pos=positive; RIF, rifampicin; SS, symptom score; TB, tuberculosis.

### Procedures

#### TB index cases

Following informed consent obtained, a questionnaire is administered to collect sociodemographic information, TB risk factors and the medical history of TB, HIV and other diseases. Two spontaneous sputum samples are obtained, of which one is for mycobacterial culturing and one for storage for performing retrospectively Molecular Bacterial Load Assay to quantify viable *Mtb* by 16s rRNA^6^; an alternative means to quantify expectorated bacterial load for an estimate of infectiousness. Both liquid and solid mycobacterial cultures are performed on decontaminated sputum samples, with all *Mtb* isolates stored at −80° for future DNA extraction and whole genome sequencing. A questionnaire on symptom duration and TB risk factors is also administered.

#### Household key informant

At baseline, a household key informant (either the TB IC or one of the HHCs) is identified and asked to answer questions of a household questionnaire that collects socioeconomic elements like structure of the house or flat, income and household assets and covariates possibly associated with risk of TB infection, for example, windows/air exchange, presence of comorbid conditions and risk factors like the source of cooking energy and properties of the household kitchen.

#### Household contacts

Informed consent is obtained from all eligible adult HHCs. For HHC <18 years of age, the guardian is asked to provide informed consent, with assent also sought from children dependent on local guidance. At baseline, a questionnaire is administered collecting information on socioeconomic and demographic characteristics, previous medical history of TB, HIV and other diseases, exposure risk factors, smoking and alcohol history. The physical examination includes height, weight, mid-upper arm circumference and blood pressure measurement. In addition, all HHCs are offered free HIV testing according to the National Guidelines. All people with confirmed HIV infection will have CD4 counts performed and be referred for TB preventive therapy. Those not yet on antiretroviral therapy (ART) and those who interrupted ART are referred for ART at local services.

Point of care HbA1c (A1cCare, SD Biosensor, Gyeonggi-do, Republic of Korea) and haemoglobin (Hemocue 301+, Hemocue, Angelholm, Sweden) tests and spirometry (including prebronchodilation and postbronchodilation with inhaled salbutamol) are performed at baseline or the 6-month visit. HHCs who did not take up HIV testing or other screening at baseline are offered these tests at each study visit. Any HHCs with test results requiring treatment or further investigations are referred for respective services.

HHCs are screened for TB using the WHO symptom screening questionnaire and a dCXR, reviewed by a clinical officer. dCXRs are not performed in pregnant HHCs. HHCs with a positive WHO symptom screening and/or abnormal dCXR are asked to provide sputum samples for TB investigations, that is, for GeneXpert and mycobacterial culture. Those with negative symptom screen and normal dCXR are asked to provide a spontaneous sputum sample for storage (with sputum induction performed if required).

At baseline, urine, serum, plasma, whole blood (native, and with RNA preservation in PAXgene tubes (BD Biosciences, New Jersey)) are stored. A finger-prick sample is taken and investigated using the Xpert TB Host Response RUO Prototype cartridge (Cepheid, Sunnyvale, California). T-cell Activation Marker Tuberculosis (TAM-TB) assay and Interferon Gamma Release Assay (IGRA; STANDARDTM F TB-Feron FIA (IFN-gamma; SD Biosensor, Republic of Korea) are performed on fresh venous blood. In Tanzania and Mozambique, storage of peripheral blood mononuclear cells for later characterisation of the TB-specific immune response is also performed.

Procedures for follow-up and unwell visits are similar to those at baseline. Measurement of HIV status, haemoglobin (HB), HbA1c, spirometry, CD4 count and IGRA testing are not performed at follow-up visits, unless not done previously. At the last scheduled visit, all HHCs not known to have HIV are reoffered HIV testing and a spontaneous or induced sputum sample is stored for all participants.

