### Novel test candidates

A range of novel test candidates targeted at pathogen detection or identification of host responses to *Mtb* are being applied, either in real-time (for all participants) or retrospectively (in a case–control design). While a number of novel test candidates have been prespecified, the ERASE-TB biobanking processes allow for addition of further candidate tests to be evaluated on stored samples as they become available.

DCXRs offer good sensitivity for diagnosis of pulmonary TB. However, high interinvestigator and intrainvestigator variability, and lack of trained interpreters presents a barrier to implementation in many high-TB burden settings. Computer-aided interpretation systems, such as CAD4TB (Delft Imaging, Hertogenbosch, Netherlands) and qXR (Qure.ai, India), may increase image-reading capacity, with good performance, and serve, therefore, as a systematic screening tool to identify individuals in need of confirmatory TB tests.^17 18^

Xpert MTB/RIF Ultra is a nucleic acid amplification test for *Mtb* with a lower limit of detection compared with the previous Xpert MTB/RIF generation, and, therefore, conferring higher sensitivity in paucibacillary specimens. This, however, comes at the expense of specificity, particularly in high TB incidence settings, resulting in ‘false positives’.^19^ WHO guidelines recommend Xpert MTB/RIF Ultra for TB diagnosis among adults and children acknowledging that further evaluation, particularly of the role of Xpert MTB/RIF Ultra for TB screening, is needed.^20 21^

FLOW-TB is an advanced ELISA for the detection of *Mtb* lipoarabinomannan (a mycobacterial cell wall component) in urinary specimens with results available within 65 min.^22^

The TAM-TB detects Mtb-specific CD4 T-cells through in vitro antigen stimulation with *Mtb*-derived peptides, that is, from ESAT-6 to CFP-10, followed by flow cytometry. TAM-TB discriminated latent *Mtb* infection from TB in freshly collected blood with 83% sensitivity and 96%–98% specificity in previous studies. Furthermore, TAM-TB may detect early TB disease progression up to 9 months prior to the identification of *Mtb* in sputum.^23–25^

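### In symptom-free contacts the clinical officer's reading of the chest film decides who is tested for TB, so CAD sensitivity on that same diagnostic-visit film is biased upward

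*Protocol article*

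**What the plan says.** Under Novel test candidates, the article says of the CAD products: "Computer-aided interpretation systems, such as CAD4TB (Delft Imaging, Hertogenbosch, Netherlands) and qXR (Qure.ai, India), may increase image-reading capacity". Their intended role is "as a systematic screening tool to identify individuals in need of confirmatory TB tests". The first primary objective is "to determine the sensitivity and specificity of novel diagnostics to detect TB, in particular, asymptomatic or minimally symptomatic TB".

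Under Household contacts, the screening rule is: "HHCs are screened for TB using the WHO symptom screening questionnaire and a dCXR, reviewed by a clinical officer". Entry to testing follows from it: "HHCs with a positive WHO symptom screening and/or abnormal dCXR are asked to provide sputum samples for TB investigations". The abstract gives the same rule: "Individuals screening positive (WHO symptom screen or dCXR) will be requested to provide sputum for Xpert MTB/Rif Ultra". For the remainder, "Those with negative symptom screen and normal dCXR are asked to provide a spontaneous sputum sample for storage". Follow-up visits are described as similar to baseline, and the sputum taken from everyone at the last scheduled visit is also for storage. The article states no testing of the stored sputum to reclassify screen-negative contacts.

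Under Statistical analyses, cases are contacts diagnosed with TB and controls are contacts who do not develop it. Sensitivity, specificity and ROC area are planned for the novel tests as a group. Endpoint assignment is blinded to the new test results. CAD is not treated differently from the blood and urine candidates.

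**The concern.** For a contact without symptoms at a scheduled visit, an abnormal human reading of the film is the only stated route to the reference test. CAD is then scored on that same image. An asymptomatic case whose film the officer called normal is not diagnosed at that visit, so it drops out of the sensitivity denominator. If CAD tends to miss the films that the officer misses, the cases removed are those on which CAD would have done worst. This is partial verification bias, and it is more direct for CAD than for blood or urine tests, which are not derived from the gating film.

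The blinding does not address this. It keeps CAD output away from those who assign endpoints, but it leaves the officer's reading as the gate.

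At stake is the CAD estimate in the group that the first primary objective singles out, and the fairness of any comparison in which algorithms containing CAD are set against others in asymptomatic contacts.

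**Working it through.** **1. The plan's own figures.** Sample size gives intervals for tests of incipient infection, with 49 incident cases and 196 controls. Exact (Clopper-Pearson) 95% intervals reproduce them to rounding:

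- 36/49 = 73.5% (58.9–85.1); stated 59–85
- 40/49 = 81.6% (68.0–91.2); stated 68–91
- 180/196 = 91.8% (87.1–95.3); stated 87–95
- 184/196 = 93.9% (89.5–96.8); stated 90–97

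Also 49 + 15 = 64, 64/2100 = 3.05% and 49 × 4 = 196. These figures are sound. They describe sampling error only and make no allowance for how cases were verified.

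**2. Inputs for the bias.** The documents supply none, so these are assumptions:

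- c, true CAD sensitivity in asymptomatic TB: 0.70
- h, officer's sensitivity in asymptomatic TB: 0.5 to 0.9
- φ, correlation of the two readings within true asymptomatic cases: 0, 0.3, 0.5

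**3. Asymptomatic cases.** Only reader-positive cases are verified, so the apparent sensitivity is P(CAD+ | reader+, TB) = p11/h, where p11 = c·h + φ·√[c(1−c)h(1−h)], capped at min(c, h).

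Largest case shown, h = 0.5 and φ = 0.5: p11 = 0.35 + 0.5·√(0.21 × 0.25) = 0.4646; divided by 0.5 this is 0.929, or +23 points.

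Smallest non-zero case shown, h = 0.9 and φ = 0.3: p11 = 0.63 + 0.3·√(0.21 × 0.09) = 0.671; divided by 0.9 this is 0.746, or +5 points.

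| h | φ = 0 | φ = 0.3 | φ = 0.5 |
|---|---|---|---|
| 0.5 | 0.700 | 0.837 | 0.929 |
| 0.6 | 0.700 | 0.812 | 0.887 |
| 0.7 | 0.700 | 0.790 | 0.850 |
| 0.8 | 0.700 | 0.769 | 0.815 |
| 0.9 | 0.700 | 0.746 | 0.776 |

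The bias vanishes at φ = 0 and shrinks as the reader misses fewer cases.

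**4. All cases together.** Let a be the asymptomatic share of true TB. Assume that symptomatic cases are all verified and that CAD sensitivity is also 0.70 in them. Apparent sensitivity = [(1−a)·c + a·p11] / [(1−a) + a·h]. With φ = 0.5:

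| a | h = 0.6 | h = 0.7 | h = 0.8 |
|---|---|---|---|
| 0.3 | 0.738 | 0.735 | 0.729 |
| 0.5 | 0.770 | 0.762 | 0.751 |
| 0.7 | 0.809 | 0.793 | 0.775 |

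A true 70% appears as about 73–81%, an overstatement of 3 to 11 points.

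**5. Where the mechanism does not reach.** Contacts with a positive symptom screen are tested whatever the film shows. Earlier films of incident cases were not selected for having been read as abnormal. Pregnant contacts have no film and lie outside any CAD analysis.

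**The case against.** The best reply has three parts.

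First, the affected slice is limited. The objective also covers minimally symptomatic TB, contacts who screen positive on symptoms are verified regardless of the film, and the article announces no separate CAD estimate for asymptomatic cases. This stands, and it is why the effect over all cases is smaller. It does not remove the effect, because film-triggered cases remain in the pooled estimate.

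Second, the size is assumed. This also stands. A reader might suppose that CAD flags 95% of TB films the officer calls abnormal but only 20–40% of those called normal, with reader sensitivity of 60–80%. True sensitivity would then be between 0.6 × 0.95 + 0.4 × 0.2 = 0.65 and 0.8 × 0.95 + 0.2 × 0.4 = 0.84, an overstatement of 11 to 30 points. Those inputs imply a correlation of 0.60 to 0.77. Nothing in the article supports agreement that close, and its own remark on high variability between and within readers points the other way.

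Third, test-specific analyses commonly sit in a full protocol or SAP, neither of which is shown. The absence of a correction is therefore not the finding. The finding is how the gate, the storage-only rule, the candidate list and the case definition, all fixed in the article, combine for this one candidate.

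A reader might also infer that the study can never show CAD finding TB that the officer missed. That does not follow. Contacts are re-screened every 6 months for 18–24 months, a case missed at one visit can be diagnosed later, and CAD can be run on the earlier film that was read as normal. The stored sputum might also supply some missing reference results, although the article states no such use.

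**Conclusion.** The concern holds for one estimate: CAD sensitivity on the diagnostic-visit film in asymptomatic contacts diagnosed at scheduled visits. There the reference standard is not independent of the candidate, and the bias is upward if CAD and reader agree positively within true cases. That is to be expected of two readings of one image, but the article does not quantify it. With true CAD sensitivity 70%, reader sensitivity 50–90% and correlation 0.3–0.5, the overstatement is about 5 to 23 points. Over all cases, at correlation 0.5 with reader sensitivity 60–80% and 30–70% of cases asymptomatic, it is about 3 to 11 points.

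A parallel charge against specificity should not be pressed. A missed case that is never diagnosed would fall into the control pool, and a CAD flag on it would count as a false positive. But only about 3% of contacts are expected to be diagnosed with TB, screening is repeated, and the documents give no basis for sizing the effect.

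This is worth correcting because it touches a primary objective and the correction is cheap. It does not call the cohort or the other candidates into question.

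**What to change.** In Statistical analyses, add the following for CAD:

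1. Report accuracy on diagnostic-visit films separately by what triggered sputum testing: a positive symptom screen, or the film alone.
2. In cases triggered by the film alone, describe the result as agreement with the human reader, not as sensitivity.
3. Assess CAD for early detection on films from visits before the diagnostic visit.
4. State this limitation wherever algorithms containing CAD are compared with other tests in asymptomatic contacts.

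The overall CAD estimate need not be confined to symptom-positive contacts: that would move it away from the population in the first objective and change the disease spectrum. Nor need CAD combinations be barred from ranking, which would cut into the third primary objective.

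The screening rule and visits stay as they are, and the trigger can be read from the symptom-screen and film data already collected. The cost is fewer cases per estimate, from an expected total of 64, hence wider intervals, and no unqualified claim of CAD sensitivity for asymptomatic TB from diagnostic-visit films.
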